### Statistical analysis

2.8

All data will be analyzed using statistical software SPSS 25.0 (SPSS Inc, Chicago, IL). Under the condition that the measurement data meet the normality and homogeneity of variance, the before and after data of the same group are compared using the paired *t* test. If the data in the group are not normal, the Wilcoxon signed rank sum test in the nonparametric test can be used. The measurement data meet the conditions of normality and homogeneity of variance, and the data of the same period between the 2 groups are compared using the independent *t* test method. If the 2 sets of data do not meet the normal distribution, the Mann-Whitney *U* test in the nonparametric test makes it easy to compare the average level of data with no statistical significance. The count data are expressed in terms of frequency (f) and composition ratio. The composition ratio or percentage is tested by *χ*^2^ test. If the theoretical frequency T < 5 but T ≥1 in the data, the *χ*^2^ test with continuity correction is used. If any theoretical number is 0, Fisher test is used. To evaluate the treatment effect, Wilcoxon signed rank sum test will be used. All tests used a 2-sided test, with *P* < .05 indicating that the difference will be statistically significant.

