#### Grouping method

2.4.2

We will be divided into awakening stroke group (wake group whose morbidity is not exact) and ischemic stroke group (the group clarifying the time of onset) according to whether the onset time of the patient is clear. The awakening group is divided into the awakening group with thrombolytic therapy and the awakening group without thrombolysis according to whether they receive thrombolytic therapy.

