## Discussion

3

Intravenous thrombolytic therapy for ischemic stroke in the ultra-early stage has been proved to be an effective treatment in most randomized trials. However, ultra-early intravenous thrombolysis has a strict treatment time window (onset time <4.5 hours). Exceeding this treatment time window will increase the incidence of symptomatic intracranial hemorrhage, and severe cases may be life-threatening. WUS starts in sleep and is a more common form of ischemic stroke. Its incidence rate can be as high as 25%.^[17]^ Since patients or witnesses cannot provide accurate time of onset, the start time of stroke is still “normal at last.” Therefore, even if the patient or eyewitness finds out, the prescribed time window has already been exceeded. However, some recent research results prove that the original method does not seem appropriate. The study by Kim et al^[18]^ also focused on patients with WUS and stroke patients with unknown onset times during the day without witnesses. He found that nearly half of WUS patients will be immediately awake as soon as clinical symptoms appeared. Roveri et al^[19]^ divided the study subjects into 2 groups, the WUS group and the intravenous thrombolysis group within 3 hours of onset. Early CT manifestations will be applied to the early CT score of the Alberta Stroke Project (ASPECTS), and it was found that regardless of the risk factors and stroke severity Or the ASPECTS score is very close between the 2 groups. There was no statistically significant difference in the early CT scan ASPECTS scores between the 2 groups, indicating that the ischemic event of WUS patients occurred shortly before awakening or awakened as soon as the disease occurred. The author also pointed out that the prognosis of patients in the intravenous thrombolysis group was significantly better than that in the WUS group. The most representative epidemiological evaluation of WUS comes from a 2-center study of 1853 patients with ischemic stroke, including 273 WUS patients. The results show that compared with non-WUS patients, the incidence of WUS patients older age and higher NIHSS score on admission. However, if the time window is not considered, 35% of the patients are suitable for thrombolytic therapy. Then, if we can more accurately assess the onset time of WUS patients, a large number of patients will benefit from thrombolytic therapy. The study found that the mismatch of DWI/FLAIR has a high specificity and sensitivity for the judgment of patients within 3 to 4.5 hours. Thomalla et al^[20]^ observed 543 patients within 4.5 hours of onset. Under the field strength of 1.5 T, the specificity of DWI/FLAIR mismatch judgment of stroke patients within 4.5 hours of onset was as high as 78%. Morelli et al^[21]^ collected 27 WUS patients and 143 non-WUS patients and received intravenous thrombolysis. The results showed that the proportion of patients with mRS ≤1 point was 36.4%. The author mentioned in the conclusion that the selected WUS patients are suitable for intravenous thrombolysis. This study is based on the previous study, and has a purposeful choice for WUS patients who are given thrombolytic therapy. The imaging findings are consistent with DWI/FLAIR mismatch. In summary, we speculate that the selected WUS patients are safer to use intravenous thrombolytic therapy, which is expected to improve the patients’ early efficacy and long-term prognosis. However, whether the statistically significant benefits can be obtained remains to be observed by expanding the sample size. There is no consistent conclusion about the pathogenesis of WUS. WUS is more likely to manifest as small vessel disease. Male patients with sleep apnea are more likely to have WUS, and frequent snoring may be one of the mechanisms of WUS pathogenesis.^[22,23]^ The incidence of WUS patients is relatively high, and the effectiveness and safety of intravenous thrombolysis under the guidance of multimodality imaging treatment of WUS need to be further explored by prospective, large-scale studies.

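### Section 2.8 lets preliminary checks choose the between-group test and assigns no test to normal data with unequal variances

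*Protocol article*

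**What the plan says.** Section 2.8 (Statistical analysis) sets out a rule for measurement data.

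- **Between groups, t test.** Both conditions must hold: "The measurement data meet the conditions of normality and homogeneity of variance, and the data of the same period between the 2 groups are compared" with the independent t test.
- **Between groups, fallback.** Non-normality is the only trigger: "If the 2 sets of data do not meet the normal distribution, the Mann-Whitney *U* test in the nonparametric test" is used. The same sentence speaks of comparing an average level.
- **Within a group.** The paired t test is also made to depend on equal variances, with the signed-rank test if the data are not normal.
- **Treatment effect.** A separate sentence reads "To evaluate the treatment effect, Wilcoxon signed rank sum test will be used".
- **Level.** "All tests used a 2-sided test, with *P* < .05 indicating that the difference will be statistically significant".

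The outcome to which the between-group rule most naturally applies is the NIHSS, scored at admission, 24 hours and 7 days (section 2.6.2). The article gives no sample size, allocation ratio or SD. Section 2.4.2 forms groups "according to whether the onset time of the patient is clear" and, within the awakening group, "according to whether they receive thrombolytic therapy". Section 2.5.2 ties that treatment to the MRI result. Sections 2.1 and 2.7 describe a randomised two-group trial with sealed envelopes.

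**The concern.** There are two separate faults.

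1. **A gap in the rule.** The t test needs normality and equal variances, while Mann-Whitney needs non-normality. Normal data with unequal variances meet neither condition. Whoever does the analysis then picks a test with the data in view. The choice can also fall differently at 24 hours and at day 7.
2. **A check that does not protect the level.** In modest samples a non-significant variance test does not show that variances are equal. If they differ and the groups differ in size, the pooled t test is off its 5% level. It is too liberal when the smaller group is more variable and too strict, with loss of power, when the larger group is. Nothing in the article fixes equal group sizes.

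Three statements in the same section add to this. The paired t test does not need equal variances; it needs roughly normal differences. Mann-Whitney does not compare averages when the spreads differ. The signed-rank test is a paired procedure and cannot compare two independent groups, so it does not fill the gap.

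**Working it through.** **The gap, from the text**

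| | Variances equal | Variances unequal |
|---|---|---|
| Normal | independent t test | no test named |
| Not normal | Mann-Whitney | Mann-Whitney |

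**Inputs for the size of the effect.** From section 2.8: two-sided 5% level and the decision rule. Assumed, because the article gives none: normal data, equal means, group sizes, SD ratios, and both preliminary checks run at 5% (Shapiro-Wilk in each group, then Levene).

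**The plan's own figure.** The only stated figure is the 5% level. With equal variances the rule reproduces it (first and sixth rows of the simulation table).

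**Large-sample check of the pooled t test, no preliminary checks**

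Size = 2·[1 − Φ(1.96·√(V_pooled/V_true))], where V_pooled = s_p²·(1/n₁ + 1/n₂), s_p² = (n₁σ₁² + n₂σ₂²)/(n₁ + n₂), and V_true = σ₁²/n₁ + σ₂²/n₂. Only the size ratio matters, so take n₁ = 1 and n₂ = 2.

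- Smaller group SD 1.25: s_p² = (1.5625 + 2)/3 = 1.1875; V_pooled = 1.1875 × 1.5 = 1.781; V_true = 1.5625 + 0.5 = 2.0625; size 6.9%.
- Smaller group SD 1.5: s_p² = (2.25 + 2)/3 = 1.417; V_pooled = 2.125; V_true = 2.75; size 8.5%.
- Larger group SD 1.25: V_pooled = 2.0625; V_true = 1.781; size 3.5%.
- Larger group SD 1.5: V_pooled = 2.75; V_true = 2.125; size 2.6%.
- Equal sizes: 5.0% at any SD ratio.

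**Simulation of the stated rule under the null, 2:1 sizes, 20,000 runs per row (all entries in %)**

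| Sizes | SD ratio; more variable group | t test reached | t rejects when reached | No-test cell | Whole rule, gap untested | Gap filled by Welch | Gap filled by Mann-Whitney | Welch throughout |
|---|---|---|---|---|---|---|---|---|
| 20 v 40 | 1 | 85.3 | 5.1 | 4.9 | 4.8 | 5.1 | 5.0 | 4.9 |
| 20 v 40 | 1.25; smaller | 72.6 | 7.0 | 17.6 | 5.8 | 6.3 | 6.4 | 4.9 |
| 20 v 40 | 1.5; smaller | 46.3 | 9.0 | 43.9 | 5.0 | 6.4 | 7.1 | 4.8 |
| 20 v 40 | 1.25; larger | 75.2 | 3.5 | 14.8 | 3.2 | 4.1 | 3.7 | 4.9 |
| 20 v 40 | 1.5; larger | 51.4 | 2.9 | 38.5 | 1.9 | 4.0 | 3.1 | 5.0 |
| 40 v 80 | 1 | 85.6 | 4.6 | 4.7 | 4.5 | 4.8 | 4.7 | 4.7 |
| 40 v 80 | 1.25; smaller | 59.8 | 7.1 | 30.4 | 4.9 | 6.0 | 6.4 | 4.9 |
| 40 v 80 | 1.5; smaller | 19.1 | 8.9 | 71.2 | 2.6 | 5.8 | 7.0 | 4.9 |
| 40 v 80 | 1.25; larger | 63.2 | 3.5 | 26.9 | 2.7 | 4.2 | 3.8 | 5.0 |
| 40 v 80 | 1.5; larger | 22.1 | 2.8 | 68.7 | 1.1 | 4.7 | 3.5 | 5.1 |

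A separate simulation at 20 v 40, with the smaller group more variable, gave 7.1% (SD ratio 1.3) and 9.5% (1.5) when the t test is reached. That is the upper end of the range quoted here.

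**Conditional rate against whole rule.** At 20 v 40, ratio 1.5, smaller group more variable, the t branch contributes 0.4632 × 0.0903 = 0.0418. The Mann-Whitney branch adds 0.0086, giving 0.0504 if the gap is left untested. Welch in the gap brings this to 0.0639, and Mann-Whitney brings it to 0.0710.

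**Other size ratios, t test when reached, SD ratio 1.25 to 1.5.** At 1.5:1 it rejects in 6.0 to 8.0% or 3.7 to 4.3%. At 3:1 it rejects in 7.6 to 11.9% or 1.9 to 3.2%. In each pair the first range has the smaller group more variable. Welch without checks lies between 4.5 and 5.9% in every scenario tried.

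**The case against.** **The size is assumed.** A reader might infer that the plan has a true error rate of 7 to 9.5%, or below 4%. The documents do not support that. They give no sizes or SDs, and those rates count only datasets that pass both checks, near 2:1. If data in the gap get no test, the whole rule at 2:1 rejects in 2.6 to 5.8% (smaller group more variable) or 1.1 to 3.2% (larger group more variable). So a large excess of false positives and an empty cell cannot both be charged to the rule as a whole. This objection stands.

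**Unequal groups are not established.** A reader might take the Discussion's "35% of the patients are suitable for thrombolytic therapy" as a 35:65 split. It describes a cited cohort with the time window ignored, not this trial's arms. The article also contradicts itself on whether groups are randomised (2.1, 2.7) or follow onset, MRI and treatment received (2.4.2, 2.5.2), and 2.3.2 makes mismatch an inclusion criterion. Equal sizes are not promised, but unequal ones are not certain. Changing the test does not settle that contradiction.

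**The t test may matter little.** NIHSS is an ordinal score and may often go to Mann-Whitney. Section 2.6.2 also defines early efficacy and prognosis as categories, and 2.8 gives the treatment effect to the signed-rank test. This limits the practical reach. It does not fill the gap, since the signed-rank test is paired.

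**Mann-Whitney's false positives.** A reader might call it a false positive when Mann-Whitney is significant although mean changes are equal. With unlike shapes the chance of a better score can truly differ, and that is what the test addresses. The fair criticism is only of its description as a comparison of averages, in a sentence that is garbled anyway.

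**An analysis plan could name the fallback.** It could, and that would close the gap. But the article states a rule, and the rule as stated is incomplete. A Welch fallback after the checks would still give 5.8 to 6.4% or 4.0 to 4.7% in the 2:1 scenarios.

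**Conclusion.** The point holds as a gap in a stated decision rule together with a weakness of preliminary testing. The gap needs no assumption. How often it would be met does: at 2:1 sizes, about 5% of datasets with equal SDs, 15 to 30% at SD ratio 1.25, and 39 to 71% at 1.5.

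The effect on the error rate is moderate and rests on assumed normal data, sizes near 2:1 and SD ratios of about 1.25 to 1.5. When the t test is reached it rejects in about 7 to 9.5% or about 3 to 4%, depending on which group is more variable. For the whole rule the figures are 4.0 to 6.4% if Welch fills the gap and 3.1 to 7.1% if Mann-Whitney does. With equal variances there is essentially no distortion. These are ranges under assumptions and not estimates of this trial's error rate. The change is worth making because a single pre-specified test removes both faults at almost no cost.

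**What to change.** In section 2.8, replace the conditional independent t test with wording such as:

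> Measurement data, including NIHSS at 24 hours and day 7, are compared between groups with Welch's unequal-variance t test and reported as a difference in means with 95% confidence interval. No preliminary test of normality or variance is made. One rank-based analysis, with deaths ranked worst, is the fixed sensitivity analysis and is reported as the probability of a better score.

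Brunner-Munzel is a suitable rank method, because it allows unequal spreads. Ranking deaths matters because Welch's test on NIHSS has no place for patients who die, and section 2.6.2 counts death by day 7 with worsening.

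Two further edits in the same section:

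- Delete the equal-variance condition from the paired t test.
- Reconcile the signed-rank sentence with the between-group rule: either confine it to within-group change or name a two-sample method for the treatment effect.

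**Cost.** A few sentences, plus a very small loss of power when variances really are equal. At an assumed 20 v 40 with equal sample variances, Welch's degrees of freedom are (1/20 + 1/40)² / [(1/20)²/19 + (1/40)²/39] = 0.005625/0.0001476 ≈ 38, against 58 for the pooled test. The critical value rises from about 2.00 to 2.02, or roughly 1%.

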#### Inclusion criteria

2.3.2

Time of onset: last appeared to be normal until symptoms will be found <12 hours and >4.5 hours;The patient was found to be awake or witnesses found neurological deficits;NIHSS score ≥4 points;No changes or early changes are insufficient to the one-third distribution area of the middle cerebral artery;DWI/FLAIR imaging performance mismatch (DWI imaging and FLAIR imaging);All other indications for intravenous thrombolysis;Patients with large vessel occlusion are treated with endovascular treatment. The treatment principles refer to “Chinese Expert Consensus on Intravascular Treatment of Acute Ischemic Stroke.”

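### The wake-up versus known-onset comparison is not randomised, yet section 2.8 tests it only with unadjusted tests, so a baseline difference may be read as a wake-up effect

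*Protocol article*

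**What the plan says.** **Tests (Protocol article, 2.8 Statistical analysis).** For measurements, "the data of the same period between the 2 groups are compared using the independent" *t* test. The fallback is a rank test: "If the 2 sets of data do not meet the normal distribution, the Mann-Whitney" *U* test. For counts, "The composition ratio or percentage is tested by" chi-square, with a continuity correction or Fisher's test for small expected counts. One sentence addresses the treatment effect: "To evaluate the treatment effect, Wilcoxon signed rank sum test will be used". The same section introduces that test for before-after data within a group, so it is a paired test. The level is two-sided 0.05. No covariate, stratum or matching is mentioned.

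**Groups (2.4.2 Grouping method).** The first split is made "according to whether the onset time of the patient is clear". The wake-up group is then split by whether thrombolysis was received. Under 2.5.2, all known-onset patients are thrombolysed, and wake-up patients are thrombolysed or not according to DWI-FLAIR mismatch or match.

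**Evidence on case-mix (3 Discussion).** From a two-center cohort of 1853 ischemic strokes, 273 of them wake-up, the article reports: "compared with non-WUS patients, the incidence of WUS patients older age and higher NIHSS score on admission". It also cites a study against patients thrombolysed within 3 hours in which risk factors, severity and ASPECTS were close.

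**Outcomes and baseline data.** NIHSS is scored at admission, 24 hours and 7 days, and mRS after discharge (2.6.2). Early efficacy is a 4-point NIHSS fall by day 7. Age is collected on admission (2.4.1).

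**The concern.** Whether onset time is known is a property of the patient. Whatever the sealed envelopes in 2.7 allocate, they cannot allocate that. The comparison of wake-up with known-onset patients, which belongs to the stated aim in the Introduction, is therefore observational, and a two-sample test of it compares the groups with whatever age and severity they bring.

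The article itself cites evidence that age and admission NIHSS may differ. Later NIHSS depends on admission NIHSS, so an unadjusted test carries a baseline gap into the outcome. At stake is the conclusion on how wake-up patients fare beside time-window patients. A shift that comes from case-mix could be reported as a feature of wake-up stroke, and the sign of the shift need not be the same for every endpoint.

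**Working it through.** The article gives no group size, standard deviation or size of baseline difference, so there is no figure of its own to reproduce. Everything below rests on assumed values and shows orders of magnitude.

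**1. Shift in NIHSS points, with no true wake-up effect.** Assume wake-up patients enter 1 to 2 points worse and that day-7 NIHSS regresses on admission NIHSS with slope 0.5 to 0.9.

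- Day-7 level: shift = gap × slope. From 1 × 0.5 = 0.5 to 2 × 0.9 = 1.8 points higher (worse) in wake-up patients.
- Change from admission: shift = gap × (slope − 1). From 1 × (0.9 − 1) = −0.1 to 2 × (0.5 − 1) = −1.0 points, a larger fall in wake-up patients.

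The same baseline gap thus works against wake-up stroke on the NIHSS level and can work in its favour on the 4-point fall. The entry criterion of NIHSS ≥4 points the same way: a patient admitted at 4 meets the fall only by reaching 0, whereas a patient admitted higher has more room.

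**2. False-positive rate of the unadjusted test.** Let the baseline gap be *d* standard deviations and the admission/day-7 correlation *r*, with equal variances. The bias is *r* × *d* SD. The rejection rate at two-sided 0.05 is Φ(*rd*/√(2/*n*) − 1.96) + Φ(−*rd*/√(2/*n*) − 1.96), with *n* per group.

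Example with *n* = 100, *d* = 0.3, *r* = 0.7: bias 0.21 SD, standard error √(2/100) = 0.141, ratio 1.485, rejection rate 31.8%.

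Over *d* = 0.2 to 0.5 and *r* = 0.5 to 0.7:

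| *n* per group | Rejection rate, nominal 5% |
|---|---|
| 30 | 6.7% to 27.3% |
| 50 | 7.9% to 41.7% |
| 100 | 10.9% to 69.7% |
| 200 | 17.0% to 93.8% |

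The rate rises with *n*, so recruiting more patients does not cure it.

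**3. Simulation check** (3000 runs each, *r* = 0.7, no true effect):

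| *n* per group | *d* | Unadjusted *t* | Change-score *t* | ANCOVA |
|---|---|---|---|---|
| 50 | 0.3 | 18.0% | 9.2% | 4.9% |
| 100 | 0.3 | 30.9% | 13.5% | 4.9% |
| 100 | 0.5 | 66.8% | 28.2% | 5.1% |

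ANCOVA on admission NIHSS holds the nominal level when the baseline gap is the only difference between the groups. Change scores do not.

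**4. Precision.** The residual variance ratio under ANCOVA is 1 − *r*². At *r* = 0.5 it is 0.75, a 25% reduction. At *r* = 0.7 it is 0.51, a 49% reduction. This applies to the linear model for NIHSS. It does not carry over to logistic models, where adjustment changes the odds ratio being estimated and does not shrink its standard error in this way.

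**The case against.** **The evidence of imbalance is thin.** It comes from an outside cohort, no size is given, and the same section cites a study with similar severity. This stands. A reader might infer that the protocol declares its own groups to be different; it does not. The point is that a difference may occur and the named tests have no means of handling it. Adjustment is sound in either case.

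**Case-mix as a spurious treatment effect.** A reader might extend the point to thrombolysed versus non-thrombolysed wake-up patients. The documents do not support this: the cited age and NIHSS finding concerns wake-up versus non-wake-up patients only. If MRI status decides treatment (2.5.2), the treated and untreated wake-up patients are separated completely by DWI-FLAIR status, and adjusting for age and NIHSS cannot repair that. If instead the envelopes allocate thrombolysis (2.1 and 2.7), unadjusted tests of that contrast are valid and merely less efficient.

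**Large vessel occlusion.** It is tempting to require it as a covariate because "Patients with large vessel occlusion are treated with endovascular treatment". But section 2.4.1 lists only unspecified imaging data, the screening MRI in 2.5.2 names DWI and FLAIR only, and the text does not say whether endovascular treatment is added to thrombolysis or replaces it. Occlusion status cannot be assumed to be available.

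**A condensed article, with an analysis plan perhaps elsewhere.** This is fair as far as silence goes, and 2.8 does not rule out adjusted analyses or say which two groups it means. But it does not stay silent on method. It names the between-group tests, and all of them are unadjusted.

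**Adjustment is not free.** This also stands. It relies on a model, gives a conditional odds ratio for binary outcomes, needs an answer for non-normal NIHSS data, and needs a rule for deaths before day 7.

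**Conclusion.** The point holds for the wake-up versus known-onset comparison. That comparison is non-randomised by construction, the tests fixed for it are unadjusted, and the article cites evidence, though mixed, that age and admission severity may differ. It is an analysis choice that should be changed.

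The size is unknown. Under the assumed gap and slope, the artefact is 0.5 to 1.8 NIHSS points in the day-7 level and 0.1 to 1.0 points the other way in the change. Under the assumed *d* and *r*, a nominal 5% test rejects 7.9% to 41.7% of the time at 50 per group. A blanket statement that the plan is biased against wake-up stroke would go too far, since the direction may reverse for the 4-point fall. Adjustment deals only with measured covariates on which the groups overlap; other differences between the groups remain.

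**What to change.** Amend section 2.8 along these lines:

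> The main wake-up versus known-onset analysis is adjusted for admission NIHSS and age: ANCOVA for NIHSS at 24 hours and at 7 days, and logistic regression for mRS 0–1, mRS 0–2 and early response. Estimates are given with 95% confidence intervals. The unadjusted tests are secondary.

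Add three short statements:

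- Whether the whole wake-up group or only its thrombolysed part is compared with the known-onset group. In the whole group, the difference in treatment under 2.5.2 is part of the contrast and the two covariates do not remove it.
- How deaths before day 7 enter the NIHSS analysis (2.6.2 already counts death as worsening), and what is done if residuals are far from normal.
- That the odds ratios are conditional on the covariates.

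Separately, sections 2.1 and 2.7 (randomised, envelopes) must be reconciled with 2.4.2 and 2.5.2 (groups by onset knowledge, treatment received and MRI status) before any analysis of thrombolysed versus non-thrombolysed wake-up patients can be specified. The adjustment above should not be offered as a remedy for that contrast.

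The cost is analysis wording only. Both covariates are already collected, and the models are standard. The price is the modest reliance on a model described above.

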#### Safety evaluation after thrombolysis

2.6.1

The occurrence time, treatment measures, and results of various adverse events such as intracranial hemorrhage, skin, gums, and digestive tract in patients undergoing thrombolytic therapy are recorded by specialized personnel. The safety of thrombolytic therapy is mainly evaluated by the incidence of intracranial hemorrhage. During thrombolysis, if there is headache, vomiting, and other suspected intracranial hemorrhage or other parts of the bleeding, stop thrombolysis immediately. At the same time, review the head CT. If there is no symptom of appeal, the head CT is reviewed 24 hours after thrombolysis. The significant deterioration of nerve function caused by intracranial hemorrhage (increased NIHSS score ≥4 points) will be considered as symptomatic intracranial hemorrhage.

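### The stated trigger for Fisher's test (an expected count of 0) can never be met in an informative table, so expected counts between 0 and 1 have no assigned small-sample test

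*Protocol article*

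**What the plan says.** Section 2.8 (Statistical analysis) of the protocol article sets three rules for count data.

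- Default: "The composition ratio or percentage is tested by" the chi-square test, with no correction named.
- Continuity-corrected chi-square: "If the theoretical frequency T < 5 but T ≥1 in the data".
- Exact test: "If any theoretical number is 0, Fisher test is used".

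The theoretical frequency is the expected count. The section also says "All tests used a 2-sided test" and sets the significance level at 0.05. It gives no condition on the total sample size.

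The most obvious sparse outcome is in section 2.6.1: "The safety of thrombolytic therapy is mainly evaluated by the incidence of intracranial hemorrhage". Section 2.4.2 forms the main groups "according to whether the onset time of the patient is clear", and splits the wake-up group by whether thrombolysis is received. Section 2.5.2 ties thrombolysis in the wake-up group to the MRI result. No group sizes, allocation ratio or event rate are given.

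**The concern.** The lower limit of 1 on the continuity-correction band implies that something different should happen below 1. The only rule that follows applies at exactly 0, a value that an expected count cannot take in a table worth testing. The band from 0 to 1 is therefore missed by both exceptions.

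If the default applies there, the uncorrected chi-square is used where its approximation is poorest. If it does not, the test has no written basis and could be chosen after the counts are seen. At stake is the reading of rare outcomes: intracranial haemorrhage, other bleeding sites, death, and uncommon items of medical history. One or two events could be reported as a significant difference between groups.

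**Working it through.** The plan gives no sample size, power or event rate, so there is no figure of its own to reproduce. From section 2.8 come the three rules, two-sided testing and alpha = 0.05. Group sizes and event rates below are assumptions.

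**1. Can the trigger be met?** Expected count T = (row total × column total) / N. It is 0 only if a row or column total is 0. With all margins at least 1, the smallest possible T is 1 × 1 / N; at N = 400 that is 0.0025. So T = 0 never occurs in an informative table.

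**2. What the uncorrected test does when T < 1.** Put all a events in the smaller group (size n1) and none in the larger (size n2), with N = n1 + n2. Then

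chi-square = N × a × n2 / (n1 × (N − a)), which is close to a × n2/n1 for large N.

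Significance needs a value above 3.84.

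- One event: n2/n1 must be about 3.8 or more.
- Two events: n2/n1 must be about 3.84/2 = 1.9 or more.
- Equal groups: T < 1 means one event in total (T = 0.5). For 50 v 50, chi-square = 100 × 50 / (50 × 99) = 1.01, P = 0.31. This can never be significant.
- 40 v 60 with two events: chi-square = 100 × 2 × 60 / (40 × 98) = 3.06, P = 0.08. Still not significant.

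**3. Individual tables.** When all events are in the smaller group and no other table is as improbable, the two-sided Fisher P is n1/N for one event and n1(n1 − 1)/(N(N − 1)) for two.

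| Table | Smallest T | Chi-square | Uncorrected P | Fisher P |
|---|---|---|---|---|
| 1/20 v 0/80 | 0.20 | 100×80/(20×99) = 4.04 | 0.044 | 20/100 = 0.20 |
| 1/10 v 0/90 | 0.10 | 100×90/(10×99) = 9.09 | 0.003 | 10/100 = 0.10 |
| 2/40 v 0/80 | 0.67 | 120×2×80/(40×118) = 4.07 | 0.044 | 40×39/(120×119) = 0.109 |
| 2/30 v 0/90 | 0.50 | 120×2×90/(30×118) = 6.10 | 0.014 | 30×29/(120×119) = 0.061 |

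The disagreement is not unlimited. For 2/20 v 0/80, Fisher gives 20×19/(100×99) = 0.038, so there both tests are significant.

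**4. Type I error of the whole rule.** This was obtained by enumerating both binomials at a common event rate. The rule as written uses the uncorrected test for 0 < T < 1, the corrected test for 1 ≤ T < 5, and the uncorrected test otherwise. The amended rule differs only in using Fisher for T < 1. Tables with no events count as non-rejection.

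| Sizes | Rate | As written | Fisher for T < 1 |
|---|---|---|---|
| 50:50 | 1–6% | 0.0–1.4% | identical |
| 40:60 | 1–6% | at most 1.3% | identical |
| 40:80 | 2% | 3.1% | 0.2% |
| 20:60 | 3% | 2.1% | 0.5% |
| 15:60 | 3% | 8.1% | 1.5% |
| 20:80 | 1% | 8.8% | 0.8% |
| 20:80 | 2% | 8.6% | 1.4% |
| 20:80 | 6% | 2.7% | 1.6% |
| 20:100 | 1% | 7.3% | 0.7% |
| 10:90 | 1–3% | 4.1–4.5% | 0.4–1.8% |
| 10:90 | 6% | 5.1% | 2.3% |

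The excess over 5% is concentrated at imbalances of about 4:1 to 5:1 with low event rates.

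**The case against.** The strongest reply is that 0 is a slip for less than 1. The preceding sentence stops at 1, so Fisher was evidently meant for what lies below, and an experienced analyst would use it there. The article also never says expressly that the band goes to the uncorrected chi-square. This is fair as to intent. It does not rescue the written rule, which leaves only the default test for that band.

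A reader might infer that the rule generally produces false significance. The figures do not support that: with equal or nearly equal groups nothing changes, and in many unequal settings the type I error stays below 5%. Even 1/10 v 0/90, the most striking single table, belongs to a setting where the overall error is close to nominal.

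A reader might also infer that the groups will be unequal and that expected counts below 1 are likely. The article describes a randomized trial with two parallel groups and gives no sizes or ratio. Formation of groups by onset status and MRI result makes imbalance possible, no more.

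Nor is symptomatic haemorrhage named as the main safety measure. Section 2.6.1 names intracranial haemorrhage and only defines the symptomatic form, which cannot be the more frequent of the two. It describes adverse events "in patients undergoing thrombolytic therapy are recorded by specialized personnel" and specifies no between-group test of bleeding. These points limit the consequence; the error in the threshold stands.

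**Conclusion.** The point holds as an error in a stated rule. The condition for Fisher's test cannot be met, and expected counts between 0 and 1 have no assigned small-sample test. That part follows from the definition of an expected count and needs no assumption.

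The consequence is conditional. It requires that the default chi-square be applied literally, that the groups be clearly unequal (from about 1.9:1 with two events, about 3.8:1 with one), and that the events fall in the smaller group. Under those conditions one or two events can be called significant against Fisher's test, and type I error reaches 8 to 9% near 4:1 with rates of 1 to 2%. Without them it changes no conclusion. Since sizes and rates are not in the article, the size of the effect in this trial cannot be stated. It is worth correcting because the rule is explicit, wrong, and cheap to mend.

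**What to change.** In section 2.8, change the Fisher condition from an expected count of 0 to any expected count less than 1. That closes the gap and leaves the continuity-corrected band as it is. A simpler alternative is Fisher's exact test whenever any expected count is below 5, which would also replace the continuity-corrected band; that is a choice of convenience, since the corrected band is not shown to be at fault. Make the change before outcome data are examined.

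The cost is one phrase or sentence. The downside is some conservatism of the exact test: at 20:80 with a 2% rate the type I error becomes 1.4%, well under the nominal 5%.
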